**Methods:**

We will conduct a hybrid type III effectiveness-implementation randomised controlled trial with economic evaluation. We will include adult individuals with chronic musculoskeletal pain, recruited from primary healthcare in the city of Guarapuava, Brazil. Individuals will be randomised to three implementation groups receiving a pain science education intervention (*EducaDo*r) but delivered in different modalities: group 1) synchronous online; group 2) asynchronous videos; and group 3) interactive e-book only. Implementation outcomes will include acceptability, appropriateness, feasibility, adoption, fidelity, penetration, sustainability, and costs. We will also assess effectiveness outcomes, such as pain, function, quality of life, sleep, self-efficacy, and adverse effects. Cost-effectiveness and cost-utility analyses will be conducted from the SUS and societal perspectives. The evaluations will be done at baseline, post-intervention (10 weeks), and 6 months.

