**Fig. 3 Fig3:**
[figure not shown]
Adaptation of Proctor’s conceptual model of implementation research

The primary implementation outcomes will be cost-effectiveness, adoption, and acceptability (satisfaction using a numerical scale from 0 to 100). Primary and secondary implementation outcomes are described below and summarized in Table 1.*Acceptability* will be analysed from the perspective of the organisation through a focus group, from the perspective of end-users through an individual qualitative interview about satisfaction with the intervention, and by a numerical scale from 0 to 100 on how satisfied they were in participating in the intervention. The acceptability of the implementation will also be evaluated by the Acceptability of Intervention Measure (AIM) [47] in organisations and end-users. The AIM has four questions with a Likert scale from 1 (completely disagree) to 5 (completely agree), and the mean of the score will be used (1 to 5). Higher scores indicate greater acceptability [47].*Appropriateness* will be analysed from the end-users’ perspective regarding the perception of the appropriateness of each component of the *EducaDor* programme about their health condition through an adapted questionnaire [48]. This questionnaire will assess the degree to which participants agree with a series of statements about the intervention, on a Likert scale from 1 (totally disagree) to 4 (totally agree). The appropriateness of the implementation will also be evaluated by the Intervention Appropriateness Measure (IAM) [47] in the organisation and end-users. The IAM score is the same as the AIM.*Feasibility* will be evaluated from the perspective of the organisation and individual providers through a focus group, and the Feasibility of Intervention Measure (FIM) [47] will be used in participants, organisations and individual providers. The FIM score is the same as the AIM and AIM.*Adoption* will be analysed by the percentage of acceptance of public health users to participate in the *EducaDor* programme referred from primary healthcare. We will contact by telephone those public health users who refuse to participate by inviting them to an individual qualitative interview to identify barriers to engagement in the *EducaDor* programme.*Fidelity* will be evaluated by an independent pain specialist ([name]), who will randomly select 10% of the recorded meetings and evaluate the intervention providers in relation to the fidelity of the intervention manuals with the content and quality of the meetings in a qualitative individual interview.The adherence of participants with the *EducaDor* programme will be measured by the frequency rate in synchronous meetings; self-rated performance of proposed homework on a numerical scale from 0 to 10 during the intervention period; and by exercise adherence scale (EARS-Br) [49].*Penetration* will be analysed descriptively from the rate of public health users referred from each primary healthcare unit.*Sustainability* will be evaluated by a focus group with public health managers after the presentation of the results of the study to discuss the maintenance of the *EducaDor* programme, and by a response rate of synchronous group users and reasons for discontinuity of the programme through an individual qualitative interview.*Costs* will be estimated from the SUS and societal perspectives in a time horizon of 6 months. The SUS costs will include the intervention costs and healthcare utilization costs covered by SUS. The intervention costs will be determined by preparation, video recording, development and editing, maintenance and support technology costs, monitoring data costs and staff, training health professionals and project management costs, number and duration of phone calls and the number of text messages sent to participants. The e-book and asynchronous intervention costs will be diluted in 10 years. The healthcare utilization costs covered by SUS will include prescribed drugs, medical consultations, physiotherapy-based care, visits to specialists, diagnostic exams, emergency services and hospitalisation. The societal costs will include the SUS costs, private healthcare costs, patient costs (out-of-pocket expenses with unprescribed drugs, complementary costs, and transportation costs), and lost productivity costs (related to absenteeism). The quantities of resource utilization will be identified by the participants in a self-rated diary cost that will be provided at baseline and an assessor will collect this information by telephone every 3 months. The healthcare utilization costs covered by SUS will be valued using the Brazilian standard costs [50]. Patient costs will be valued using the out-of-pocket expenses reported by patients. Private transportation will be valued by the price of Brazilian gasoline per kilometre and public transportation by the reference price of Guarapuava city. The lost productivity costs will be estimated from the hours of absenteeism to work (paid and unpaid) through a questionnaire, and evaluated according to the Human Capital Approach and will be valued using gender-specific price weights [50].

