#### Sample size estimation

The sample size was estimated by simulation [61, 62]. The sample size simulation was performed in four steps: (1) defining the sample size problem and outcomes; (2) defining, writing and running the sample size simulation algorithm; (3) estimating the possible outcomes derived from the simulations; (4) finding the optimal sample size.

In step 1, the sample size problem was developed considering the following objective: to estimate the minimum sample size required to comply with a maximal type I error (*α*) of 0.05 or 5% and a maximal type II error (*β*) of 0.20 or 20%. The input outcomes were: populational mean pain intensity (0–10) of 6.0 with a standard deviation (SD) of 2.3; a hypothesised minimal clinically important difference (MCID) in pain intensity between groups of -1.0 with an SD of 0.25 [63]; three groups; three repeated measurements (baseline, 10 weeks and 6 months); a correlation within the repeated measurements of 0.30 or 30% [64]; a minimum of 30 participants per cluster (five physiotherapy facilities); a correlation within clusters of 0.20 or 20% [65]; and a loss to follow-up of 30% [66].

In step 2, the simulation algorithm was defined and written in R language [67]. The input outcomes defined in step 1 were then included in the algorithm. Normal distributions were simulated using the input means and SDs set in step 1 as hyperparameters. The simulations were gathered running the distributions considering several possible sample sizes for one group ranging from 5 to 5000 in 32 steps (i.e., 5 to 50 by 5; 60 to 100 by 10; 150 to 500 by 50; 600 to 1000 by 100; and 2000 to 5000 by 1000), with 100 replications for each step, and repeating this procedure 10 times (i.e., 10 iterations), summing up 32,000 sample size simulations in total.

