#### Economic evaluation

The economic evaluation will be conducted with an ITT approach. The cost-effectiveness analysis will be conducted using pain (measured by the numerical pain scale after 6 months of randomization). The cost-utility analysis will be conducted using quality-adjusted life-years (QALYs). The QALYs will be estimated from the evaluation of the health status of the participants using the EQ-5D-3L instrument. These health states of the descriptive system of the EQ-5D-3L will be converted into utility values using Brazilian tariffs [54]. Finally, the QALYs will be calculated from the linear interpolation between measurement points using the utility values of the participants collected at baseline, 10 weeks, and 6 months after randomization.

The average cost differences between groups will be calculated for SUS and societal perspectives and disaggregated by cost categories. The average cost and effect differences will be estimated by unrelated regression analyses. The incremental cost-effectiveness ratios will be calculated by the difference between the costs of the interventions divided by the difference between the effects of these interventions. Bias-corrected and accelerated bootstrapping techniques (5000 replications) will be performed to estimate the uncertainty surrounding cost difference and incremental cost-effectiveness ratios. The cost-effectiveness pairs from the 5000 replications will be presented graphically in a cost-effectiveness plane. Cost-effectiveness acceptability curves will be estimated to indicate the probability of interventions being cost-effective compared to each other at different willingness-to-pay thresholds [70].

Multiple imputations by chained equations will be used to handle the missing cost and effect data. An imputation model will be developed and will include sociodemographic and anthropometric variables, duration of symptoms and all available values of costs and effects measured at baseline and follow-up periods. Ten complete datasets will be created (considering loss of efficiency < 5%). The grouped estimates will be calculated according to Rubin’s rules [71].

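### BCa bootstrapping is planned for the ICER itself; if the effect difference between the active arms is small, an interval built that way can fall well short of its nominal coverage

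*Protocol article*

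**What the plan says.** All of this is in the protocol article; no separate analysis plan is at hand.

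- **Definition of the ICER (Economic evaluation).** "The incremental cost-effectiveness ratios will be calculated by the difference between the costs of the interventions divided by the difference between the effects". The effect is pain on the numerical scale at 6 months for cost-effectiveness, and QALYs for cost-utility.
- **Method for its uncertainty (Economic evaluation).** "Bias-corrected and accelerated bootstrapping techniques (5000 replications) will be performed to estimate the uncertainty surrounding cost difference and incremental cost-effectiveness ratios". The method is named for two targets, the cost difference and the ICER.
- **Other displays (Economic evaluation).** The replicate cost-effect pairs are to be plotted on a cost-effectiveness plane, and acceptability curves drawn over a range of willingness to pay.
- **Comparators (Abstract, Methods).** "Individuals will be randomised to three implementation groups receiving a pain science education intervention". There is no inactive control.
- **Standing of the outcome (Implementation outcomes).** "The primary implementation outcomes will be cost-effectiveness, adoption, and acceptability". Table 1 names the ICER as the cost-effectiveness indicator.

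The section gives no confidence level for the ICER, and no rule for an effect difference that is near zero or changes sign.

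**The concern.** BCa takes the ordered bootstrap values of an estimator and shifts the percentiles used as limits. The shift depends on a bias term, set by where the observed value ranks among the replicates, and on an acceleration term. This works when the estimator varies smoothly. A ratio does not: as its denominator passes through zero it jumps from a very large positive to a very large negative value. Replicates that cross zero effect land at the far end of the ordering, and the bias term reads that displacement as bias.

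A separate problem is interpretation. A positive ratio can mean dearer and better or cheaper and worse; a negative one can mean dominant or dominated. Any ICER interval, BCa or not, mixes these when the effect difference changes sign.

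The setting makes this a practical matter. All arms receive the e-book, weekly messages and physiotherapy, and the video and e-book arms also share an introductory pain-education session. The Discussion expects two of the three modes to be the most cost-effective, so a clear separation of every pair is not presumed. At stake is the stated precision of the main figure for a primary implementation outcome that is meant to inform health managers.

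**Working it through.** **Inputs from the protocol (Sample size estimation).** Pain: "populational mean pain intensity (0–10) of 6.0 with a standard deviation (SD) of 2.3". Planning difference: "a hypothesised minimal clinically important difference (MCID) in pain intensity between groups of -1.0 with an SD of 0.25". 80 per group before corrections, 105 after; 30% loss to follow-up.

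**Assumed, because the protocol does not give them.** A 95% level; true pain differences below 1.0; cost differences of 0 to 0.6 cost SDs; normal or lognormal costs (coefficient of variation 1); cost-effect correlation of 0 or 0.3.

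**1. The plan's own figure.** It states no coverage for the ICER, so the nearest check is its sample size. With 80 per group, 1.0 point, SD 2.3 and two-sided 5%, power = Φ(1.0 / [2.3 × √(2/80)] − 1.96) = Φ(2.75 − 1.96) = 0.785, close to the intended 80%. Also 80 × 1.3 = 104, close to 105. The inputs are therefore read correctly.

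**2. Distance of the denominator from zero.** SE of a pairwise pain difference = 2.3 × √(2/n).
- n = 105: 0.317
- n = 74 (105 × 0.7 = 73.5): 0.378

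The chance that the estimated difference has the wrong sign is Φ(−δ/SE). At n = 105 this is 26% for δ = 0.2, 17% for 0.3, 5.8% for 0.5 and 0.1% for 1.0.

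**3. What the bias term does.** Suppose the observed pain difference is 0.3 at n = 105 and the cost difference is clearly positive. About 17.2% of replicates have the opposite effect sign; their ratios are negative and all rank below the observed one. The share below is then about 0.5 + 0.172 = 0.672, so z0 = Φ⁻¹(0.672) = 0.446. With zero acceleration the limits are taken at Φ(2 × 0.446 − 1.96) = 14% and Φ(2 × 0.446 + 1.96) = 99.8%, in place of 2.5% and 97.5%. The correction cuts off one tail of the replicate distribution because of the jump at zero effect, not because the estimator is biased.

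**4. Coverage by simulation.** Each scenario had 2000 trials, 2000 bootstrap replicates resampled within arm, and normal costs. The table gives the percentage of 95% intervals that exclude the true ICER, as the range over cost differences of 0 to 0.6 SD. The net-benefit column is the test of cost difference − ICER × effect difference = 0, which avoids the division.

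| n per arm | True pain difference | BCa | Percentile | Net benefit |
|---|---|---|---|---|
| 105 | 0.2 | 23-37 | 0-4 | 5-6 |
| 105 | 0.3 | 18-27 | 0-3 | 5-6 |
| 105 | 0.5 | 10-14 | 1-3 | 5-6 |
| 105 | 1.0 | 4-5 | 3-5 | 5-6 |
| 74 | 0.2 | 23-40 | 0-5 | 5-6 |
| 74 | 0.3 | 20-30 | 0-4 | 5-6 |
| 74 | 0.5 | 13-20 | 1-3 | 5-6 |
| 74 | 1.0 | 4-6 | 2-3 | 4-6 |

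Monte Carlo error is about 1 percentage point at a 37% miss rate: √(0.37 × 0.63 / 2000) = 0.011.

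**5. Sensitivity.** With 5000 replicates at n = 105, across normal costs, lognormal costs, correlation 0.3 and a pain SD of 2.19, the BCa miss rate was 26-38% at 0.2 points, 9-15% at 0.5 and 3-6% at 1.0. Setting the acceleration to zero hardly changed these figures, so the bias correction is responsible. A separate run with gamma costs and a cost difference of 1-2 standard errors gave 28-34% at 0.2, 23-27% at 0.3, 12-16% at 0.5 and 4-5% at 1.0.

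**The case against.** The strongest reply is that the protocol never promises a 95% ICER interval. It speaks of estimating uncertainty, its only stated 95% level in the analysis sections is for the mixed-model differences, and the next sentence puts the replicate pairs on a plane. On that reading BCa serves the cost difference, and the plane and curves show the uncertainty of the ICER. The part about the level stands: 95% is inferred. The rest does not fit the sentence, which names the ICER as a target of BCa. BCa adjusts interval limits and does nothing to a scatter plot.

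Other points stand:
- Differences of 0.2-0.5 points are not planning values, and at the one that is (1.0), coverage is near nominal.
- The cost inputs are assumed, and the simulations leave out clustering, multiple imputation and regression estimation. QALYs as the denominator were not simulated.
- Percentile intervals use the same ordered ratios and do not under-cover from 0.2 to 0.5 points. The shortfall therefore cannot be blamed on the ordering of ratios alone.
- The acceptability curve already carries net-benefit information and the plane already shows the quadrants, so part of the remedy repackages planned output.

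A reader might infer that managers would be unable to tell a better and dearer mode from a worse and cheaper one. The documents do not support that, because the planned plane shows exactly this.

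**Conclusion.** The point holds in a limited form. BCa is a poor choice for the uncertainty of the ICER in this trial. If a 95% interval is meant, it would miss the true ratio in roughly 10-38% of trials at 105 per arm when the true pain difference is 0.2-0.5 points, and in up to about 40% with 74 observed per arm. At 1.0 point it misses in about 5%. The cause is the BCa bias correction acting on a ratio whose denominator can cross zero. The mixing of quadrants is a second, distinct weakness that percentile limits share.

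A reader might go on to infer that the cost-effectiveness analysis as a whole is invalid, or that this trial's ICER interval will fail at these rates. Neither follows. BCa is acceptable for the cost difference, and the plane and acceptability curves remain valid. The miss rates depend on a true difference and on cost inputs that the protocol does not state. The change is still worth making: the ICER will be calculated whatever effect is observed, small differences are plausible between three active modes, and cost-effectiveness is a primary implementation outcome.

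**What to change.** In the Economic evaluation section:

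1. Restrict BCa bootstrapping to the cost difference and the effect difference.
2. Report each ICER as a point estimate, with the share of the 5000 replicates in each quadrant of the plane.
3. Replace any ICER interval with a bootstrap interval, at a stated level, for incremental net monetary benefit (threshold × effect gain − cost difference). Give it for each pairwise comparison over the willingness-to-pay range already planned for the acceptability curves, with effect gain defined as pain reduction or QALYs gained.

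Moving to percentile limits for the ICER would repair the coverage in the range examined but not the mixing of quadrants.

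The cost is a rewording of one sentence. The same replicates are reused and no new data are needed. The small downside is that net benefit is shown over a range of thresholds, not as a single interval.

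### The imputation model listed for the economic evaluation does not name randomised arm; followed as written, it pulls between-arm differences towards zero

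*Protocol article*

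**What the plan says.** The Economic evaluation section states: "Multiple imputations by chained equations will be used to handle the missing cost and effect data". It then describes the model, which "will include sociodemographic and anthropometric variables, duration of symptoms and all available values of costs and effects measured at baseline and follow-up periods". Allocated arm belongs to none of these classes. Neither arm as a predictor nor imputation by arm appears there, in the Missing data section, or elsewhere in the article. The number of imputations is justified in the words "Ten complete datasets will be created (considering loss of efficiency < 5" (a percentage).

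The analysis that uses the imputed data compares arms: "The average cost and effect differences will be estimated by unrelated regression analyses". No covariates are named for these regressions. For utilities, "the QALYs will be calculated from the linear interpolation between measurement points using the utility values of the participants collected at baseline" and at the two follow-ups. The effect measure for cost-effectiveness is pain at 6 months.

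The economic section gives no expected missing rate. The only such figure is in Sample size estimation, whose list of inputs ends "and a loss to follow-up of 30" (per cent). Cost-effectiveness is one of the three primary implementation outcomes under Implementation outcomes.

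**The concern.** An imputation model should contain every variable in the analysis model, above all the exposure. If arm is left out, two participants with the same covariates and different allocations receive imputed values from the same distribution. Their outcomes then contribute little or nothing to the arm contrast, and the pooled difference moves towards zero. This happens even when data are missing completely at random.

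The stakes are the incremental effects, the incremental costs and the acceptability curves behind a primary implementation outcome. The main mixed model contains group, time and their interaction, so the trial could also report two different 6-month pain effects from the same participants. Neither planned sensitivity analysis would show the problem. One removes e-book and video development costs and the other restricts to participants with high adoption; neither changes the imputation.

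**Working it through.** **The plan's own figure.** Loss of efficiency with m imputations is 1 - 1/(1 + FMI/m), where FMI is the fraction of missing information. With m = 10:
- FMI 0.30: 1 - 1/1.03 = 2.9%
- FMI 0.50: 1 - 1/1.05 = 4.8%
- 5% is reached only near FMI 0.53

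The stated loss below 5% reproduces. Ten imputations are not the problem, and more of them would not cure an omitted predictor.

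**Inputs for the size of the shrinkage**, all from Sample size estimation:
- "populational mean pain intensity (0–10) of 6.0 with a standard deviation (SD) of 2.3"; the SD is used here
- "a hypothesised minimal clinically important difference (MCID) in pain intensity between groups of -1.0 with an SD of 0.25"; the difference of -1.0 is used here
- correlation between repeated measurements 0.30
- 105 participants per group

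Assumptions added here: the difference of -1.0 is present at both 10 weeks and 6 months, data are missing completely at random, and the imputation model has no proxy for arm.

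**Expected result by hand.** Let p be the fraction with imputed 6-month pain.
- Both follow-ups missing: imputation rests on baseline pain, which is balanced by randomisation, so the contrast among imputed participants is about 0. The overall contrast is (1 - p)(-1.0), which is -0.70 at p = 0.30 and -0.90 at p = 0.10.
- Only 6 months missing: the 10-week value carries part of the arm effect. Its regression coefficient, given baseline, is r/(1 + r) = 0.30/1.30 = 0.23. The contrast is (1 - p)(-1.0) + p(0.23)(-1.0). At p = 0.30 this is -0.70 - 0.07 = -0.77; at p = 0.10 it is -0.92.

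**Simulation.** Three arms of 105, 10 Bayesian linear-regression imputations, 600 replications, Monte Carlo SE about 0.011 to 0.016, true contrast -1.00, correlation 0.30:

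| Missing | Pattern | Arm omitted | Arm included |
|---|---|---|---|
| 10% | both follow-ups | -0.90 | -0.99 |
| 10% | 6 months only | -0.93 | -1.01 |
| 20% | both follow-ups | -0.78 | -1.01 |
| 20% | 6 months only | -0.86 | -0.98 |
| 30% | both follow-ups | -0.70 | -0.97 |
| 30% | 6 months only | -0.78 | -0.99 |

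At an assumed correlation of 0.60, the 30% rows with arm omitted become -0.71 and -0.81. Shrinkage at 30% missing is therefore about 19% to 30%. A separate two-arm simulation (500 replicates, correlation 0.30, 30% missing) gave -0.68 and -0.76 with arm omitted, and -0.99 and -1.03 with it included.

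**Weight of baseline utility in the QALY.** Taking 6 months as 26 weeks, linear interpolation gives baseline utility a weight of 0.5 x 10/52 = 0.096 year. As a share of the 0.5-year horizon this is 0.096/0.5 = 19%. Suppose a chance baseline imbalance of 0.03 in utility. Without adjustment, the direct contribution to the QALY difference is 0.03 x 0.096 = 0.003. If later utilities correlate 0.6 with baseline, it is 0.03 x [0.096 + 0.6 x (0.250 + 0.154)] = 0.010. The imbalance and this correlation are assumptions.

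**The case against.** The list is introduced as what the model will include, not as all that it will include. A condensed article may name auxiliary variables and leave arm implicit. That stands: the omission of arm is the natural reading of a detailed list, not a stated exclusion, and the finding is conditional on the list being followed.

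The list contains all observed costs and effects. Intervention cost may be known for dropouts and may differ by arm, so it can act as a partial proxy. In a three-arm simulation at 30% missing with assumed cost levels, an always-observed intervention cost brought the contrast back to between -0.89 and -1.04 when the synchronous arm's cost was well separated. When that cost lay between the other two, recovery was little or none (-0.70 to -0.83). The figures in the table are therefore near the unfavourable end. The proxy is too uncertain to rely on when arm itself is available.

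Several stronger readings are tempting and are not supported:
- A reader might infer that 30% of costs and effects will be missing. The 30% is a sample-size allowance. Costs come from participant diaries, databases and a provider survey, and no missing rate is given for them.
- A reader might infer that QALYs are compared without baseline utility. The article names no covariates for the economic regressions and never says baseline utility is left out. Baseline adjustment is promised in Quantitative data analysis, though in the mixed-model paragraph. This is silence that a fuller plan may fill.
- A reader might infer that leaving centre unlisted biases the results. Individuals are randomised within centre, so the omission mainly affects precision.
- A reader might infer a known bias in the ICER. None was computed. If the effect shrinks to -0.70 and the cost difference does not shrink, the ratio is inflated by 1/0.70 = 1.43. If both shrink by the same fraction, it is unchanged.

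**Conclusion.** The point holds in conditional form. The article specifies the imputation model in enough detail to name anthropometric variables, yet omits the exposure on which every incremental estimate depends. If followed as written, and without a useful proxy for arm, the 6-month pain contrast shrinks by roughly the missing fraction when both follow-ups are missing, and by somewhat less when the 10-week value is observed. On the planning inputs that means about 22% to 30% at 30% missing and about 7% to 10% at 10% missing. Including arm removes essentially all of this.

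The sizes rest on data missing completely at random, normal pain scores and an equal effect at both follow-ups. Costs, QALYs and ICERs were not simulated; the direction of the bias carries over to cost and QALY differences, but its size there is not established. The correction should be made before analysis, because nothing else planned would reveal the bias.

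**What to change.** State that randomised arm enters every chained equation, or that imputation is run separately within arm, and add physiotherapy centre as the stratification factor. Including arm as a predictor is enough for the main contrast. Imputing within arm is more flexible, but about 105 participants per arm may call for a leaner predictor list. Allocation and centre are known for everyone from randomisation, so the cost is a sentence in the plan and a few lines of code.

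As a clarification rather than a correction, state that the QALY regression adjusts for baseline utility and the pain regression for baseline pain. Both are already collected.
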